## Background

Approximately 800 women die in pregnancy or childbirth every day [1]. Obstetric haemorrhage (antepartum and postpartum), sepsis and hypertension in pregnancy account for more than 50% of maternal deaths worldwide, 99% of which occur in low- and middle-income countries (LMICs) [1]. Early detection and effective management of these conditions relies on vital sign monitoring, including pulse and blood pressure [2]. Strategies aiming to improve the detection of haemodynamic instability are vital in recognising women in need of urgent medical care.

There are simple, cost-effective and established interventions to save lives for each of these pregnancy-related conditions, but the barrier to initiating treatment lies in recognition of maternal haemodynamic compromise and access to interventions [3, 4]. Accurate blood pressure measurement is essential for detecting and monitoring pre-eclampsia, enabling antihypertensive and prophylactic anticonvulsant therapy, appropriate transfer to higher-care facilities for timed delivery and, thereby, prevention of maternal and perinatal mortality and morbidity; however, the majority of blood pressure devices that are commercially available either fail validation in pregnancy or their accuracy is unknown [5]. In LMICs, hypertension is frequently under-detected, not only because of poor availability of working and accurate blood pressure devices, but also because of inadequate training [6, 7]. Vital sign measurement is equally critical in the management of obstetric haemorrhage and sepsis [2]. Postpartum haemorrhage, the leading cause of maternal mortality in LMICs [1], can cause death within a few hours, but effective interventions are available and early recognition facilitating immediate intervention is often lifesaving [8].

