#### Secondary outcomes

Maternal deaths from all causes were collected with additional information regarding the cause of maternal death collected to determine the potential for impact of the CRADLE VSA. The percentage of deaths that occurred as a result of obstetric haemorrhage, pregnancy-related sepsis and hypertensive disorders of pregnancy will be presented across all clusters pre and postintervention with adjusted risk ratios (RRs). If there are other large groups of other clinically important causes of death, e.g. early pregnancy complications, these will also be defined.

Maternal secondary outcome measures:Intensive care unit admission, defined as any admission to a specific intensive care unit or an equivalent highest-level care environment within the trial area (or referral to the highest level care facility outside of the area) in areas where an intensive care unit does not existStroke, defined as hemiparesis and/or blindness developed during pregnancy or in the 42 days postpartum lasting longer than 48 hCause of intensive care admissionCause of maternal deathCause of emergency hysterectomyPlace of eclamptic fitPlace of maternal death

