### Statistical plan

The effect of the intervention on the primary outcome, on each of the three components, and on the secondary outcomes specified above, will be reported. Results will be reported firstly as odds ratios (ORs), with risk ratios (RRs) as a secondary comparison if the appropriate models converge. Within the stepped-wedge cluster design it remains appropriate to analyse outcome data from clusters individually, despite randomising cluster time points with some clusters paired [17].

The main statistical analysis method will be by logistic regression, using generalised estimating equations with a population-averaged model [18] (Stata command xtgee) with fixed centre effects and separate fixed linear trends in each centre for changes in outcome over time. Autoregressive correlation will account for decreasing correlations between observations over time. This model outperformed the multilevel model structure of Hussey and Hughes [19], being apparently less susceptible to bias. It gives equal weight to each woman, rather than each centre, and (being population-averaged) reports effects averaged over the length of the trial. Simulations studies suggest that using time categories, rather than linear trends do not correct well for separate time trends by centre, and can cause convergence problems. Results will be expressed as ORs; at the low event rates expected (≤ 5%), ORs and RRs are reasonably close (in the simplest case, for 5% and 3.75%, RR = 0.75, OR = 0.74). A secondary analysis to obtain RRs using a log link will be attempted, but simulation studies suggest that the convergence may be poor. We will adjust for centre effects and linear time trends and the interaction between them. This will effectively adjust for differences in baseline availability of resources between clusters.

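### Cause-of-death percentages: adjusted risk ratios are promised outright in one section and only if a model converges in another, and an odds ratio cannot stand in for them

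*Protocol article*

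**What the plan says.** Two sections of the protocol article set the effect measure for the same outcome.

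- **Secondary outcomes.** The measure has deaths as its denominator: "The percentage of deaths that occurred as a result of obstetric haemorrhage" is the first item, and the sentence goes on to the other two causes: "pregnancy-related sepsis and hypertensive disorders of pregnancy will be presented across all clusters pre and postintervention with adjusted risk ratios (RRs". No condition is attached. Cause of maternal death is also in the list of maternal secondary outcomes.
- **Statistical plan, scope.** "The effect of the intervention on the primary outcome, on each of the three components, and on the secondary outcomes specified above, will be reported". This takes in the cause-of-death comparison.
- **Statistical plan, reporting rule.** "Results will be reported firstly as odds ratios (ORs), with risk ratios (RRs) as a secondary comparison if the appropriate models converge".
- **Statistical plan, route to the RR.** "A secondary analysis to obtain RRs using a log link will be attempted, but simulation studies suggest that the convergence may be poor". No other way of obtaining an RR is named.
- **Statistical plan, defence of the OR.** At the expected event rates, up to 5%, "ORs and RRs are reasonably close". The example given is 5% against 3.75%, with RR 0.75 and OR 0.74.

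The only figure for the size of the shares is in the Background. There, haemorrhage, sepsis and hypertension taken together "account for more than 50% of maternal deaths worldwide".

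**The concern.** One section commits to an adjusted RR for the cause-of-death percentages. The other makes every RR conditional on a fit whose convergence it doubts. If that fit fails, an analyst following the Statistical plan is left with an OR, and an analyst following the Secondary outcomes section still owes an RR with no stated way to obtain it.

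The plan's reassurance about the OR does not fill the gap. It is an argument about rare events per delivery, whereas this outcome is a share of deaths. The protocol collects cause of death to judge how far the device could have had an effect. An OR read as a risk ratio would therefore exaggerate the shift in the very causes the device targets.

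**Working it through.** **Inputs**

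- Rates of 5% and 3.75%, with RR 0.75 and OR 0.74: Statistical plan.
- Primary outcome 1% falling to 0.75%: Sample size calculation.
- Combined share of the three causes above 50%, worldwide: Background.
- Baseline share of deaths of 20% to 60%: my assumption, since the documents give no shares for these clusters.
- RR of 0.75 for the shares: taken from the plan's own example, for illustration only.

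**Formula.** With baseline p1 and p2 = RR × p1, OR = [p2/(1 − p2)] / [p1/(1 − p1)].

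**Step 1: the plan's own figure.** (0.0375/0.9625) / (0.05/0.95) = 0.7403, which rounds to the stated 0.74. The example is correct.

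**Step 2: the primary outcome.** (0.0075/0.9925) / (0.01/0.99) = 0.748, against an RR of 0.750. The OR is harmless here.

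**Step 3: shares of deaths, RR held at 0.75.**

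| Baseline share p1 | p2 | OR |
|---|---|---|
| 20% | 15% | 0.706 |
| 30% | 22.5% | 0.677 |
| 40% | 30% | 0.643 |
| 50% | 37.5% | 0.600 |
| 60% | 45% | 0.545 |

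At 50%, for example, (0.375/0.625) / (0.50/0.50) = 0.600. Read as an RR, that is a 40% reduction where the actual one is 25%.

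**Step 4: the reverse.** For a given OR, p2 = OR × odds1 / (1 + OR × odds1), where odds1 = p1/(1 − p1), and RR = p2/p1. A reported OR of 0.75 means an RR of 0.752 at a 1% baseline, 0.789 at 20%, 0.857 at 50% and 0.882 at 60%.

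**Step 5: the two rules side by side.**

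| | Secondary outcomes | Statistical plan |
|---|---|---|
| Measure for cause-of-death shares | adjusted RR | OR first, RR second |
| Condition | none | model must converge |
| Method for the RR | none named | log link, convergence doubted |
| Range in which OR ≈ RR is argued | not addressed | 5% or less |

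If the log-link model does not converge, both columns cannot be honoured.

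**The case against.** The strongest reply is that the Secondary outcomes section is the more specific text and so governs this comparison, that the article never says an OR will replace the promised RR, and that the choice of model family and fallback belongs in an analysis plan that is not shown. An OR labelled as an OR is also not wrong.

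Much of this stands, and it rules out several stronger readings that a reader might infer:

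- *That the plan expects its RR model to fail.* It says only that the model will be tried and that convergence may be poor.
- *That RRs are promised throughout.* For the primary outcome, its components and the other secondary outcomes they are secondary and conditional. Only the cause-of-death sentence is unconditional.
- *That a misleading OR will be substituted.* The text does not say so. The plan limits its closeness argument to low rates and does not extend it to shares of deaths.
- *That the doubtful model is log-binomial and breaks because fitted probabilities approach 1.* The article names a log link but no family, and a share of 50% to 60% is not near 1.
- *That the trial's shares exceed 50%.* That figure is worldwide and for three causes combined. Single causes will be lower, and at 20% the gap is modest (OR 0.71 against RR 0.75).

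The reply does not remove the mismatch. The article itself fixes the measure, the link, the convergence condition and the low-rate argument, and its general rule expressly takes in the secondary outcomes. Treating the specific sentence as governing still leaves the doubted fit as the only named route to the RR.

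**Conclusion.** The point holds as a narrow inconsistency. The unconditional promise of adjusted RRs for cause-of-death percentages and the conditional rule in the Statistical plan do not agree, and the 5% argument does not cover shares of deaths. Over an assumed 20% to 60% baseline, an RR of 0.75 corresponds to an OR of 0.71 to 0.55. An OR is therefore not an acceptable approximation to the promised RR.

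The size depends on the assumed baseline and on the shares being analysed with deaths as the denominator, as the Secondary outcomes section states. If each cause were analysed per delivery, rates would be low and the two measures close. The matter is minor: it concerns a supporting secondary outcome and leaves the primary conclusion untouched.

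**What to change.** Reconcile the two sections with one prespecified rule. For the cause-of-death percentages, and for any other outcome analysed as a share of cases (such as causes of intensive care admission or hysterectomy, or place of fit or death, if handled that way):

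1. Obtain the adjusted RR by marginal standardisation from the planned logistic model. Fit it among the cases, predict each case's probability with the intervention term set on and then off, average each set, and take the ratio. This needs no log-link fit.
2. Allow a Poisson-family log-link model as an alternative only with a small-sample correction to the robust variance, because there are just ten clusters and the model carries centre-specific trends.
3. State that ORs are not used as approximate RRs for these outcomes.

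The cost is a sentence or two in the plan and slightly more analysis work, with no new data. The primary OR analysis, the reporting of rare outcomes, the sample size and the power do not change.

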## Discussion

We have described the protocol for a mixed-methods, multicentre, stepped-wedge cluster-randomised controlled trial. The main objective of this trial is to determine whether the introduction of the CRADLE intervention (CRADLE VSA device and CRADLE training package) to maternity care settings in LMIC communities and facilities reduces maternal mortality and morbidity. A stepped-wedge cluster-randomised controlled trial design has been chosen to evaluate the intervention in a pragmatic fashion. Individual randomisation would be logistically difficult and would not measure impact and transferability at a population level. The stepped-wedge design is useful where phased implementation is preferable because of logistical and practical constraints.

The CRADLE intervention is intended to be beneficial to all types of practice in a wide variety of settings. In keeping with the pragmatic trial design, and to ensure that results are generalisable, efforts were made to ensure that participating clusters represented diverse settings, at both a country level with different healthcare systems and at a facility level. Our study clusters, therefore, included academic/specialist facilities, private facilities and primary and secondary-level government facilities. We hypothesise that the intervention will work by facilitating earlier detection, referral and treatment of pregnancy complications.

A composite of maternal mortality or morbidity (one of maternal death, eclampsia or emergency hysterectomy with no double counting) was chosen as the primary outcome as powering a trial for maternal death alone would require a prohibitively large sample size. These are robust and meaningful clinical endpoints that are unambiguous and, therefore, feasible to collect in these environments. Maternal complications were selected, each of which is associated with significant acute and chronic morbidity. Therefore, a reduction in this composite would be highly desirable. Each component of the primary outcome will be individually interrogated to ensure no paradoxical effects within the composite, i.e. an increase in morbidity may be associated with a reduction in mortality, as a consequence of intervention. Therefore, should the CRADLE intervention result in appropriate referral and intervention (e.g. hysterectomy) this will be recognised as beneficial even though the overall effect on the composite outcome may be neutral. We have ensured that all primary outcome measures are feasible to collect at primary to tertiary facilities, as determined through the feasibility study. It is, therefore, not necessary to conduct costly household surveys. In the unlikely event that a primary outcome occurs without HCP contact, this is likely to be unchanged pre and post intervention and should not affect our ability to assess the impact of intervention implementation.

It is recognised that the CRADLE intervention may reduce perinatal mortality and morbidity. Perinatal outcomes have not been included as primary outcomes as the intervention is designed specifically to identify maternal health complications. Many of these occur postpartum and will not directly influence perinatal outcomes. Acquisition of detailed perinatal data within LMIC settings would be a substantial additional cost. However, the secondary perinatal outcomes will be collected in women who experience a primary outcome.

The potential for this trial to demonstrate reductions in maternal mortality and morbidity and a positive impact on the working lives of HCPs will be of interest to local, national and international health-policy makers. The CRADLE VSA could become a key tool in achieving the post-2015 global maternal health goals, as well as facilitating a basic recommended standard of care, i.e. accurate blood pressure determination in all pregnant women. Given the low cost, reliability and accuracy of the device, if the trial is successful, a low regulatory hurdle and rapid progression to adoption is anticipated. The trial results will be generalisable beyond the immediate research setting, as the trial will be carried out in a variety of countries and at both at community and facility levels. A robust scale-up strategy will be required to support international scale-up to allow widespread and equitable access to the innovation. This will require appropriate resourcing to include commercial expertise and facilitate partnership between inventors, manufacturers and governments to maximise effective and efficient marketing, supply and distribution through appropriate channels and fair pricing.

## Trial status

Ongoing

## Abbreviations

cHCPs: Community healthcare providers
CRADLE: Community blood pressure monitoring in Rural Africa and Asia: Detection of underLying pre-Eclampsia and shock
fHCPs: Facility healthcare provider
HCP: Healthcare provider
LICs: Low-income countries
LMICs: Low- and middle-income countries
VSA: Vital Signs Alert
